## Abstract

**Background:**

Currently, the long-term prognosis and survival rate of patients with high-grade glial tumors remains poor and there are no biomarkers. hPG_80_ (circulating progastrin) secreted into the blood by tumor cells has been widely studied in colorectal cancer. Its involvement in tumorigenesis has been demonstrated in the literature. Moreover, according to a recent study, hPG_80_ is expressed in the blood of cancer patients at a significantly higher concentration than in the control group composed of healthy blood donors.

**Methods:**

The PROGLIO study is a pilot, single-center, longitudinal study that primarily seeks to evaluate circulating plasma hPG_80_ concentrations over time in patients with high-grade glial tumors. A fasting blood sample will be taken on the start and end day of radiotherapy and during the adjuvant chemotherapy (every 3 cycles). Follow-up monitoring will be performed for 9 months, with a blood sample taken every 3 months on the day of the follow-up MRI. The study plans to recruit 30 patients and recruitment started in February 2022.

**Trial registration:**

ClinicalTrials.gov, ID NCT05157594; registered on October 27, 2021.

## 1. Introduction

Since 2016, glial tumors have been classified *via* a new approach, which combines histo-pathological and molecular features (1). This classification has been recently updated. The 2021 fifth edition introduces major changes that advance the role of molecular diagnostics in central nervous system tumor classification (2). In addition, this classification enables the aggressiveness of the tumor to be assessed. The most aggressive tumors are classified as high-grade gliomas, i.e., WHO grade 3 and 4, and have a poor prognosis with an estimated 5-year survival of 30% for grade 3 and < 5% for grade 4 (3). Indeed, the long-term prognosis and survival rate for patients with high-grade glial tumors remains poor (4).

The *GAST* gene codes for a 101-amino acid precursor peptide, preprogastrin, which generates progastrin after several post-translational modifications. This 80-amino acid pro-hormone is then cleaved by pro-hormone convertases and carboxypeptidases to form glycine extended gastrins (G34-Gly and G17-Gly). These glycine ends then serve as substrates for peptidyl-α-amidating monooxygenases, resulting in the formation of the two biologically active majority forms of gastrin in the G-cells of the antrum of the stomach, controlling acid secretions during digestion: G34-NH2 for 34-amino acid gastrin and G17-NH2 for 17-amino acid gastrin (5, 6). In a pathological situation, the disruption of the Wnt/ß-catenin pathway in cancer induces the activation of the expression of the *GAST* gene coding for progastrin and its secretion in circulating form known as hPG_80_ (7). Its role has been widely studied in colorectal cancer. Thus, its involvement in the formation of cell junctions, in the inhibition of apoptosis, in the regulation of cancer stem cells, in angiogenesis and in the regulation of the Wnt signaling pathway, has been demonstrated in the literature (8–13). Furthermore, progastrin has been shown to be a factor in radio-resistance (14). An increase in *GAST* gene expression has been observed after irradiation. On the other hand, targeting hPG_80_ induces an increase in radiation-induced apoptosis. A decrease in hPG_80_ expression increases radiation-induced DNA damage and leads to the inhibition of the AKT and ERK pathways, induced by irradiation (14).

A prospective study, which was analyzed retrospectively, was performed on a total of 1,546 patients and 557 healthy blood donors, enabling the determination of hPG_80_, with the DxPG80 IVD ELISA kit developed by BIODENA CARE (15). In this study, the levels of hPG_80_ (circulating progastrin) were determined in 11 different epithelial and non-epithelial cancers (colorectal, breast, uterus, ovary, prostate, kidney, pancreas, esophagus/stomach, liver, melanoma and lung). Median hPG_80_ concentrations across cancer types were all above the limit for detection (1.2 pM) and the limit for quantification (2.3 pM). When all the cancer types were combined, the median hPG_80_ concentration was 4.88 pM. The median hPG_80_ concentration in the healthy blood donors was 1.05 pM. This study demonstrates that hPG_80_ is expressed in the blood of patients with all types of cancers at significantly higher concentrations than in a control group of healthy blood donors (7). In addition, a retrospective study of 143 patients with metastatic kidney cancer found that hPG_80_ was detected in 94% of the patients (16). More recently, a retrospective study of 168 patients with hepatocellular carcinoma found that hPG_80_ was detected in 84% of the patients (17).

As hPG_80_ is involved in many signaling pathways, which are themselves involved in the tumorigenesis of many different types of cancers, it is justifiable to assume that hPG_80_ will be measurable in patients with high-grade brain tumors. In addition, BIODENA CARE has preliminary data on IDW-wild type glioblastoma treated with radio-chemotherapy, published on a poster at the annual ASCO meeting this year (18). After surgery, hPG80 was detected in 48 (69%) patients (hPG80+) with a median concentration of 9.52 pM (IQR 5.21–21.20). This data confirms the detection of hPG_80_ in these tumors and a decrease in that marker after total tumor resection. This data provides a strong basis to reasonably hypothesize that hPG_80_ is measurable in the blood of patients with high-grade brain tumors. Furthermore, there is no routine use of a blood biomarker for glial tumors. This justifies the interest of conducting a study assessing plasma hPG_80_ concentrations in patients with high-grade brain tumors.

## 2. Methods and analysis

### 2.1. Study design

The PROGLIO study is a pilot, single-center, longitudinal study aiming to evaluate plasma hPG_80_ concentrations over time in patients with high-grade brain tumors.

This study has been registered on Clinicaltrials.gov (NCT05157594). A maximum of thirty patients are expected to be enroled. The study was started in February 2022 with an 18-month enrolment period and an estimated completion date by February 2025.

### 2.2. Study objectives and endpoints

#### 2.2.1. Main objective and endpoint

The main objective of the study is to evaluate the plasma levels of hPG_80_ (circulating progastrin) during therapeutic follow-up and relapse monitoring among patients with high-grade glial tumors.

The primary endpoint is hPG_80_ plasma concentrations measured by BIODENA CARE using their DxPG80 IVD ELISA kit, from inclusion to the last follow-up.

#### 2.2.2. Secondary objectives

The secondary objectives are:

– To study hPG_80_ concentrations according to tumor progression using the Response Assessment in Neuro-Oncology (RANO) criteria, which take progression objectified by imagery, clinical status and level of steroid therapy into account.– To evaluate the sensitivity to irradiation of hPG_80_ concentration variations.– To compare hPG_80_ plasma levels in patients, and to study inter-individual variations before, after and during disease management.

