### 2.4. Intervention

Eligible patients will be included during a consultation with an investigator after verification of their compliance with the inclusion and non-inclusion criteria (and signing of informed consent).

A fasting blood sample will be taken on the start and end day of radiotherapy and during adjuvant chemotherapy (every 3 cycles). Follow-up monitoring will be performed for 9 months, with a blood sample taken every 3 months on the day of the follow-up MRI.

Pseudonymized blood samples will be stored at the Centre Jean PERRIN and then sent to the Hospices Civils de Lyon (France) for analysis. The blood samples will be analyzed to evaluate the plasma concentrations of hPG_80_ in pmol/L using the ELISA DxPG80 kit (BIODENA CARE, France).

The risks or constraints appear minimal for the subjects participating in the study since the only interventions are blood tests.

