**Clinical evaluation**							
Medical & surgical history	✓						
History of the disease	✓						
Previous and concomitant treatments	✓	✓	✓	✓	✓	✓	✓
Toxicity evaluation (NCI CTCAE v5.0)	✓	✓	✓	✓	✓	✓	✓

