### 2.7. Sample size

The PROGLIO study is a pilot, single-center, longitudinal study whose primary objective is to describe plasma hPG_80_ concentrations over time, in patients with high-grade brain tumors. At the present time, there are no published results on the expected distributions of plasma hPG_80_ concentrations during patient follow-up in the study population, hence the pilot aspect of our study, thus no power analysis is possible for the necessary sample size estimation. A sample size of 30 patients seems generally appropriate considering the state of recent literature. On the basis of preliminary data (currently confidential being consolidated for publication), we can at least estimate that the sample size of 30 patients should enable us to ensure 80% power (5% alpha risk, two-tailed test) to show an effect size of 0.75 of the difference between high-grade brain tumors and control values (healthy subjects) in the literature (16). The preliminary results were stratified by type of surgery (biopsy, partial resection, and total resection), and no gender differences were observed.

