### 2.8. Data analysis

The main analysis consists of the descriptive analysis of plasma prograstin concentration values at each time point. For the third secondary objective, this analysis will be further developed by taking into account the longitudinal character of the data and by modeling data using mixed effects regression models, associated with graphical representations of individual trajectories.

The study of the relationship between hPG_80_ concentrations and tumor evaluation according to the RANO criteria (secondary objective 1) at different time points will be performed using generalized linear mixed models with response as the dependent variable, with hPG_80_ concentration as a fixed effect (as well as possibly other covariates), and with random effect calculations enabling the modeling of repeated data during follow-up.

The impact of radiotherapy on the variations in hPG_80_ concentrations (secondary objective 2) will be investigated using linear mixed models, followed, if relevant, by a *post-hoc* analysis by paired sample comparison tests.

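### Secondary objective 2 attributes to irradiation a within-patient change that the design cannot separate from other influences over the radiotherapy period

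*Protocol article*

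**What the plan says.** All references are to the protocol article.

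- **Objective.** Section 2.2.2 lists as the second secondary objective: "To evaluate the sensitivity to irradiation of hPG_80_ concentration variations".
- **Analysis.** Section 2.8 restates this as the effect of radiotherapy on hPG80 variation, which "will be investigated using linear mixed models, followed, if relevant", by post-hoc paired comparisons. No model terms are listed for this objective. For the RANO model, the same section allows a fixed effect of hPG80 "as well as possibly other covariates".
- **Sampling.** Section 2.4: "A fasting blood sample will be taken on the start and end day of radiotherapy and during adjuvant chemotherapy (every 3 cycles", and then every 3 months in follow-up. In Table 2 the inclusion column has no hPG80 assessment; the first is at the first radiotherapy session.
- **Population.** Table 1 admits patients due to start radiotherapy, chemotherapy or both. No unirradiated comparison is planned.
- **Surgery.** The Introduction says the preliminary glioblastoma data show "a decrease in that marker after total tumor resection". Section 2.7 adds: "The preliminary results were stratified by type of surgery (biopsy, partial resection, and total resection".
- **Data collected.** Table 2 records medical and surgical history at inclusion and "Previous and concomitant treatments" at every visit.

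**The concern.** The wording of the objective and of its analysis names a cause. What the trial observes is a change in one group of patients between the first and last radiotherapy sessions, with later samples after that. Without an unirradiated comparison, and without an earlier sample to show the trend before radiotherapy, anything else that moves hPG80 in those weeks is counted as radiation.

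The article itself points to two candidates: chemotherapy, which eligibility allows together with radiotherapy, and surgery, after which the marker is said to fall. The Introduction also cites work in which *GAST* expression rises after irradiation. A coincident fall from another cause could hide such a rise, and a coincident rise could imitate it. At stake is what the trial may conclude on this objective, not the primary description of hPG80 over time.

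**Working it through.** **1. The plan's own figure.** Section 2.7 gives 30 patients, 80% power, two-sided 5% and an effect size of 0.75 against healthy controls. Assuming two equal groups:

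n per group = 2 × (1.96 + 0.84)² / 0.75² = 2 × 7.85 / 0.5625 = 27.9, so 28.

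The t-test version gives 28.9 per group, and 81.5% power with 30 per group. The figure reproduces on that reading, but it compares patients with healthy subjects and has no bearing on objective 2.

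**2. What the within-patient change contains.** For patient i, on a suitable scale:

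- start of radiotherapy: Y0 = b + s + e0
- end of radiotherapy: Y1 = b + s + R + C·c + k + e1

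Here b is the patient's level, s a stable effect of the type of surgery, R the radiation effect, and C the effect of concurrent chemotherapy (c = 1 if given, otherwise 0). The term k is any post-surgical change still under way, and e0 and e1 are errors. Then

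Y1 − Y0 = R + C·c + k + (e1 − e0).

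The stable term s cancels; C and k do not. The mean change estimates R + C·p + mean(k), where p is the share receiving concurrent chemotherapy. One observed mean cannot be divided among three causes.

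**3. How often another cause would look like radiation.** The document gives no values for C, k or p, so these are assumptions. Setting: 30 patients, R = 0, effects in units of the SD of the change, paired t-test at two-sided 5%, 20,000 simulated trials.

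| Assumed scenario | Mean apparent change | Declared significant |
|---|---|---|
| Stable surgery differences only | 0.00 | 5.1% |
| Concurrent chemotherapy effect −0.5 in 80% of patients | −0.40 | 55% |
| Concurrent chemotherapy effect −0.5 in all | −0.50 | 75% |
| Continuing post-surgical decline −0.5 in all | −0.50 | 75% |
| Both, in all patients | −1.00 | 99.9% |

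For scale, 30 pairs have 80% power to detect a change of 0.53 SD. The negative signs are also assumed; in a two-sided test positive shifts would be declared equally often.

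**4. The same point as a ratio.** Suppose hPG80 changes by a factor r over the radiotherapy weeks, only in a fraction f of patients and not because of radiation. The overall geometric mean ratio, end to start, is r^f.

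| r (assumed) | f = 20% | f = 40% | f = 60% |
|---|---|---|---|
| 0.5 | 0.87 | 0.76 | 0.66 |
| 0.8 | 0.96 | 0.91 | 0.87 |

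**5. Would adjustment solve it?** If every patient receives concurrent chemotherapy, c = 1 throughout, and R and C cannot be separated. If 80% receive it, 30 × 0.2 = 6 patients inform the radiation-only change. Its standard error rises from 1/√30 = 0.18 to 1/√6 = 0.41 SD.

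**The case against.** The strongest reply is that this is a secondary objective in a descriptive pilot, reported in a condensed article. The Discussion asks only whether the marker is measurable and defers clinical value to further research. Several parts of the reply stand.

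- A reader might infer that the planned model leaves out surgery and chemotherapy. The article does not show this. Section 2.8 lists no terms for the model, and covariates are ordinarily left to the full protocol or the SAP.
- A reader might infer that surgical effects in general are credited to radiation. They are not: if surgery precedes both samples, a stable effect cancels. Only a change still under way matters, and the Introduction gives no time course for the fall. Preliminary results stratified by type of surgery suggest different levels, not different slopes.
- Post-surgical sampling and radio-chemotherapy are described for the preliminary cohort. For PROGLIO patients the article does not state the interval from surgery, or that chemotherapy is given during radiotherapy.
- Nothing restricts the mixed model to the first two samples.

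What does not stand is that the SAP could settle the matter. Covariates cannot supply a comparison group or an earlier sample. The later samples all follow radiotherapy, so they show no prior trend. A patient treated with chemotherapy alone would have no sample at the radiotherapy time points in Table 2. The causal wording is fixed in this document.

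**Conclusion.** The point holds as one of attribution. As worded in sections 2.2.2 and 2.8, objective 2 credits radiation with a change that may have other causes, and the design offers no means of separating them. Concurrent chemotherapy, or a post-surgical decline still in progress, could be reported as a radiotherapy effect.

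The size is unknown. The 55% to 99.9% false-attribution rates rest on assumed shifts of 0.4 to 1.0 SD, and the ratios of 0.66 to 0.96 on assumed changes in part of the sample.

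A reader might go further and say that the bias runs in a predictable direction and would mask a rise in the marker. The document does not support this: it gives no direction for a chemotherapy effect on hPG80, and does not say that a post-surgical fall continues into radiotherapy. The point is a cheap improvement to a secondary objective; it leaves the primary endpoint untouched.

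**What to change.** In sections 2.2.2 and 2.8, restate objective 2 and its conclusion as the change in hPG80 over the radiotherapy period, with or without concurrent chemotherapy, rather than as an effect of irradiation.

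As an exploratory description, present that change by type of surgery (biopsy, partial, total), time since surgery and concurrent chemotherapy. Surgical history and treatments are already recorded under Table 2; this assumes that the history includes the date and extent of surgery.

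If a term is modelled, use surgery-by-time or time since surgery. A surgery main effect adjusts only levels, which cancel anyway. Do not rely on a chemotherapy term if nearly all patients receive it.

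The cost is a more modest conclusion and small, imprecise subgroups among at most 30 patients. No extra visits, samples or patients are needed.

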### 2.3. Participant eligibility

The inclusion and non-inclusion criteria are presented in Table 1.

**Table 1 T1:** Section criteria.

**Inclusion criteria**	**Non-inclusion criteria**
Female or male 18 years of age or older.	Patient under guardianship or curatorship.
Patients with a high-grade primary glial tumor (Astrocytoma grade 3; Glioblastoma; Anaplastic Oligodendroglioma).	Psychological disorder *(cognitive disorders, vigilance disorders, etc.)* or social reasons *(deprivation of liberty by judicial or administrative decision)* or geographical reasons that could compromise the medical follow-up of the trial.
Patients scheduled to begin radiotherapy and/or chemotherapy.	Refusal to participate.
Able to give informed consent to participate in the research.	Pregnant or breastfeeding woman.

Patients with a high-grade glial tumor (glioblastomas IDH-wt, astrocytomas IDH mutated grade 3 and 4, oligodendrogliomas grade 3 and 4), who need to start radiotherapy and/or chemotherapy, will be eligible for the protocol.

### 2.4. Intervention

Eligible patients will be included during a consultation with an investigator after verification of their compliance with the inclusion and non-inclusion criteria (and signing of informed consent).

A fasting blood sample will be taken on the start and end day of radiotherapy and during adjuvant chemotherapy (every 3 cycles). Follow-up monitoring will be performed for 9 months, with a blood sample taken every 3 months on the day of the follow-up MRI.

Pseudonymized blood samples will be stored at the Centre Jean PERRIN and then sent to the Hospices Civils de Lyon (France) for analysis. The blood samples will be analyzed to evaluate the plasma concentrations of hPG_80_ in pmol/L using the ELISA DxPG80 kit (BIODENA CARE, France).

The risks or constraints appear minimal for the subjects participating in the study since the only interventions are blood tests.

### 2.5. Measures of hPG80 levels in blood samples

The ELISA DxPG80 lab kit (BIODENA CARE, France) will be used to measure hPG_80_ levels in all plasma EDTA samples according to the manufacturer's instructions. The analytical performances of the kit have been described by Cappellini et al. (15). In brief, the limit of detection (LoD) is a hPG_80_ concentration of 1 pM and the limit of quantitation (LoQ) is a hPG_80_ concentration of 3.3 pM. The inter- and intra-assay coefficients of variation (CV%) are below 10%. No cross-reactivity has been detected with gastrin-17, Gastrin-Gly or CTFP (C-Terminus Flanking Peptide). No cross-reactivity has been detected with other blood biomarkers such as CA125, CEA or PSA. No interference has been detected with chemicals such as SN-38, 5-FU or triglycerides, cholesterol or hemoglobin.

### 2.6. Study procedures and participant timeline

The overview of study assessments and procedures are presented in Table 2.

**Table 2 T2:** Data collection schedule.

		**Active treatment phase**			**Follow-up**		
	**Inclusion**	**Radiotherapy *(1st session)***	**Radiotherapy (Last session)**	**Adjuvant chemotherapy (Every 3 cycles)**	**3 months**	**6 months**	**9 months**
Information and consent	✓						
**Clinical evaluation**							
Medical & surgical history	✓						
History of the disease	✓						
Previous and concomitant treatments	✓	✓	✓	✓	✓	✓	✓
Toxicity evaluation (NCI CTCAE v5.0)	✓	✓	✓	✓	✓	✓	✓
**Biological examination**							
hPG80 plasma level assessment		✓	✓	✓	✓	✓	✓
**Tumor evaluation**							
MRI (rano evaluation)		✓	✓^*^	✓	✓	✓	✓

* Optional: If performed in standard practice.

### 2.7. Sample size

The PROGLIO study is a pilot, single-center, longitudinal study whose primary objective is to describe plasma hPG_80_ concentrations over time, in patients with high-grade brain tumors. At the present time, there are no published results on the expected distributions of plasma hPG_80_ concentrations during patient follow-up in the study population, hence the pilot aspect of our study, thus no power analysis is possible for the necessary sample size estimation. A sample size of 30 patients seems generally appropriate considering the state of recent literature. On the basis of preliminary data (currently confidential being consolidated for publication), we can at least estimate that the sample size of 30 patients should enable us to ensure 80% power (5% alpha risk, two-tailed test) to show an effect size of 0.75 of the difference between high-grade brain tumors and control values (healthy subjects) in the literature (16). The preliminary results were stratified by type of surgery (biopsy, partial resection, and total resection), and no gender differences were observed.

### 2.8. Data analysis

The main analysis consists of the descriptive analysis of plasma prograstin concentration values at each time point. For the third secondary objective, this analysis will be further developed by taking into account the longitudinal character of the data and by modeling data using mixed effects regression models, associated with graphical representations of individual trajectories.

The study of the relationship between hPG_80_ concentrations and tumor evaluation according to the RANO criteria (secondary objective 1) at different time points will be performed using generalized linear mixed models with response as the dependent variable, with hPG_80_ concentration as a fixed effect (as well as possibly other covariates), and with random effect calculations enabling the modeling of repeated data during follow-up.

The impact of radiotherapy on the variations in hPG_80_ concentrations (secondary objective 2) will be investigated using linear mixed models, followed, if relevant, by a *post-hoc* analysis by paired sample comparison tests.

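### The main analysis summarises hPG80 visit by visit with no within-patient measure, so if loss is related to hPG80 its summaries can shift, down or up, although no patient has changed

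*Protocol article*

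**What the plan says.** The primary endpoint (2.2.1) is the plasma hPG80 concentration "from inclusion to the last follow-up", and Sample size (2.7) describes a study "whose primary objective is to describe plasma hPG_80_ concentrations over time". Samples are due at the first and last radiotherapy sessions, every three cycles of adjuvant chemotherapy, and at 3, 6 and 9 months of follow-up (2.4 and Table 2).

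Data analysis (2.8) fixes the main analysis: "The main analysis consists of the descriptive analysis of plasma prograstin concentration values at each time point". It then continues: "For the third secondary objective, this analysis will be further developed by taking into account the longitudinal character of the data". That extension uses mixed effects models "associated with graphical representations of individual trajectories". Secondary objective 1 (RANO response) is given generalized linear mixed models. Secondary objective 2 (radiotherapy) is given linear mixed models, with paired tests afterwards if relevant. No longitudinal method is attached to the main analysis.

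The Introduction gives "an estimated 5-year survival of 30% for grade 3 and < 5% for grade 4". Study design (2.1) gives an "18-month enrolment period and an estimated completion date by February 2025". The section on risk of bias (2.10) deals with selection at inclusion and with undiagnosed second cancers, and does not mention death or loss during follow-up.

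**The concern.** The primary question is longitudinal, but the analysis that answers it is a series of separate summaries. hPG80 is a blood measurement, so a patient who has died or left the study contributes nothing at later visits. With the prognosis stated in the Introduction, the set of patients at the last visit may differ considerably from the set at the first radiotherapy session.

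A difference between an early and a late per-visit median therefore mixes two things: change within patients, and change in who is being measured. The article gives some reason to think that the two could be entangled. It calls progastrin a factor in radio-resistance (Introduction) and reports a lower marker after total resection. If patients with high values were lost earlier, late medians would fall and could be read as a response to treatment. If patients with low values were lost earlier, they would rise. The per-visit table alone cannot show which has happened.

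**Working it through.** **The plan's own figure.** Section 2.7 states 80% power with 30 patients for an effect size of 0.75 (two-sided 5%). A two-sample t test needs 29 per group and has 81.5% power at 30 versus 30, so the figure reproduces. It concerns a comparison with healthy controls and does not bear on this point.

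**Check 1: selection by death alone**

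Inputs from the article:
- 5-year survival: 5% in grade 4 (the article says below 5%, so this is the favourable limit) and 30% in grade 3.
- Horizon: 9 months is the stated length of follow-up. 18 months is the time from the end of recruitment (August 2023) to completion (February 2025). It is a limit on the calendar, not a visit time.
- SD of log hPG80 from the glioblastoma data in the Introduction (IQR 5.21 to 21.20 pM among detected): ln(21.20/5.21) / (2 × 0.6745) = 1.403/1.349 = 1.04.

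Assumptions: constant hazards; a hazard ratio (HR) of 1.2, 1.5 or 2.0 per SD of log hPG80; an upper log SD of 1.42; each patient's hPG80 constant over time.

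Overall survival at t months is S = (5-year survival)^(t/60):
- Grade 4: 0.05^(9/60) = 0.638; 0.05^(18/60) = 0.407.
- Grade 3: 0.30^(9/60) = 0.835; 0.30^(18/60) = 0.697.

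Let z be standardised log hPG80, normal with mean 0 and SD 1. Individual survival is exp(−H × HR^z), with H chosen so that the average over z equals S. The survivors' mean is m = E[z × exp(−H × HR^z)] / S, found by numerical integration. Their geometric mean relative to the full cohort is exp(SD × m).

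| Grade | Months | HR | m | Apparent fall, SD 1.04 to 1.42 |
|---|---|---|---|---|
| 4 | 9 | 1.2 | −0.081 | 8% to 11% |
| 4 | 9 | 1.5 | −0.175 | 17% to 22% |
| 4 | 9 | 2.0 | −0.279 | 25% to 33% |
| 4 | 18 | 1.2 | −0.161 | 15% to 20% |
| 4 | 18 | 1.5 | −0.339 | 30% to 38% |
| 4 | 18 | 2.0 | −0.516 | 42% to 52% |
| 3 | 9 | 1.2 | −0.033 | 3% to 5% |
| 3 | 9 | 1.5 | −0.072 | 7% to 10% |
| 3 | 9 | 2.0 | −0.119 | 12% to 16% |
| 3 | 18 | 1.2 | −0.065 | 7% to 9% |
| 3 | 18 | 1.5 | −0.142 | 14% to 18% |
| 3 | 18 | 2.0 | −0.228 | 21% to 28% |

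With HR 1.0, m = 0 and there is no shift. With HR below 1, m is positive and the geometric mean rises.

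**Check 2: loss of any kind, with undetectable values included**

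This used 20,000 simulated trials of 30 patients, each patient constant over time. In each trial 69% were detectable on average (log-normal, median 9.52 pM, IQR as above) and the rest were below 1 pM. Loss was logistic in hPG80 rank, with the loss fraction and the odds ratio (OR) per SD as assumptions. The starting median is about 5.1 pM. The late median is:

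| Lost | OR 0.5 | OR 1 | OR 1.5 | OR 2 | OR 3 |
|---|---|---|---|---|---|
| 20% | 6.32 | 5.09 | 4.45 | 4.04 | 3.62 |
| 30% | 6.92 | 5.16 | 4.13 | 3.56 | 2.93 |
| 40% | 7.60 | 5.12 | 3.81 | 3.03 | 2.28 |
| 50% | 8.42 | 5.14 | 3.45 | 2.57 | 1.56 |

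For OR 1.5 to 3 the apparent fall is 13% to 70%, or 8% to 36% if every patient is detectable. At 30% loss and OR 2, 90% of trials show a lower late median. The ratio to each patient's own first sample is 1 in every scenario, because no patient changes.

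**The case against.** The strongest reply is that most of the remedy is already planned. Section 2.8 extends the same analysis, for the third secondary objective, to mixed models and individual trajectories. Change under radiotherapy, which is the change most likely to be misread, has its own linear mixed model with possible paired tests. A reader might infer that the plan lacks within-patient analysis, or keeps it for one secondary objective. Neither is so: all three secondary objectives have mixed models. What stands is narrower. The main result carries no within-patient measure, although its question is about time.

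A reader might also infer that the main analysis will show a false decline because high hPG80 predicts early death. The documents do not say that it does. The Discussion treats the study as proof of concept that the marker is measurable and leaves the prognostic role to a larger study. Radio-resistance and the fall after total resection make the link plausible, not established.

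The upper figures depend on the 18-month limit and the largest assumed hazard ratio. The article gives neither a dropout rate nor the number of chemotherapy cycles before follow-up, and it enrols a mix of grades.

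Handling of missing data may sit in an analysis plan that is not shown, and its absence here is no fault. The per-time-point main analysis, however, is stated in the article. Nor is a mixed model a complete answer, since it needs an assumption about missingness and implicitly carries trajectories past death.

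**Conclusion.** The point holds in a limited form. The stated main analysis cannot separate change within patients from change in the set of patients, and the prognosis quoted in the article makes the second a real possibility. The direction is open, and the size cannot be determined from the documents. If higher values go with earlier death, the survivors' geometric mean would be lower by the 8% to 52% (grade 4) or 3% to 28% (grade 3) set out above. Those ranges rest on constant hazards, the assumed hazard ratios and the upper log SD. They illustrate sensitivity and do not predict the trial's result. The planned secondary analyses reduce the risk of misreading but do not put a within-patient measure into the main result. The study's descriptive, pilot status does not remove the point, since a within-patient change is just as descriptive and needs no test or larger sample.

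**What to change.** Keep the per-visit table and add to the main analysis:

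- at each visit, the number of patients sampled and the ratio of hPG80 to each patient's own first sample among those sampled. The first sample is the right reference because patients may start radiotherapy and/or chemotherapy (2.3);
- at each visit, first-sample values of those still sampled against those lost;
- the already planned individual trajectories and mixed model, presented with the main result as the description of the time course. State that the model assumes missingness at random and does not describe values after death.

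The cost is some wording and a few table columns, with no extra blood samples or visits. Within-patient summaries will be less precise at late visits, where fewer patients remain. Values below the detection limit need a stated convention for the ratio, since 31% of patients (100% − 69%) were undetectable in the preliminary data. Splitting losses into deaths and withdrawals would need vital status, which Table 2 does not list but the full protocol may.
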